## Abstract

**Background:**

Pathologic studies have shown that in patients with critical limb threatening ischaemia (CLTI) medial arterial calcifications are frequently found and may be responsible for aggravating the disease. These extensive calcifitcations are found not only in arteries of the leg but also in the coronary arteries and the aorta. The progression of these calcifications is fast and they stiffen the vessel wall and may thus increase the cardiovascular risk.

Reduction of progression of calcification may not only reduce the burden of CLTI but may also reduce the high residual cardiovascular risk. Medial calcifications have been halted by etidronate in other trials. Its potential to reduce the burden from peripheral vascular disease in CLTI and residual cardiovascular risk remains to be established.

**Methods:**

This is an investigator-initiated multicenter, double blind, placebo-controlled, randomized trial comparing the effects of etidronate versus placebo in patients with CLTI.

Subjects will be randomized to either treatment with etidronate for 12 months (cyclical 20 mg/kg for 2 weeks on and 10 weeks off) orally or placebo for 12 months (in a similar routine).

The primary endpoint is the change in arterial calcification as quantified by CT-scan.

Secondary endpoints are the number of amputations above and below the ankle**,** mortality, number of vascular interventions and quality of life.

**Discussion:**

Up to now, the inert end stage of vascular disease in patients with CLTI, has been considered calcification of vessel walls. We believe there is reason to reverse causation and hypothesize that calcification causes vascular disease. This reversal can be proven in a clinical trial if halting the calcification process improves the outcome of the patient. Therefore we use etidronate, a bisphosphate that has proven to stop the calcification in several rare monogenetic calcifying diseases. We aim to perform this mechanistic proof-of-concept study hopefully leading to a clinical outcome study later on.

## Background

CLTI is the most severe type of peripheral vascular disease. Patients with CLTI have pain at rest and skin wounds in the leg(s). In addition, the cardiovascular mortality is high. A recent systematic review and meta-analysis on the outcome of conservative treatment of CLTI patients showed that within 1 year of diagnosis 18% of the patients died and 27% underwent amputation. The one year amputation free survival rate was 60% (Spreen et al. 2016; Van Reijen et al. 2021). In addition, the PADI-trial reported a 10-year survival of only ±20% (Konijn et al. 2020b).

With an estimated yearly incidence of 500–1000 new cases per million individuals in Western society, CLTI poses a considerable burden on patients’ health and resources (Teraa et al. 2016).

Several histopathologic studies of amputated legs of CLTI patients have shown that calcification of the media is present in up to 72% of patients and that the classical atherosclerotic disease is less pronounced (O’Neill et al. 2015; Soor et al. 2008) In a group of 54 CLTI patients, we reported that virtually all had severely calcified peripheral vessels, coronary arteries and a severely calcified aorta. The median coronary artery calcium score was 1485 and in 19 of 45 (35%) patients, it was above 2000. The thoracic and the abdominal aorta where completely annular calcified in 37%, 31% of cases respectively.

Although treatment of CLTI has improved, there still is a high cardiovascular mortality. Current treatment strategies target on luminal thrombosis and cholesterol-driven atherosclerosis, a process mainly located in the intima. However, a process which co-occurs with atherosclerosis, arterial calcification, may independently lead to vascular disease. Arterial calcifications, especially when located in the media, are a cause of vascular stiffening and an independent cause of vascular disease (Konijn et al. 2021; Konijn et al. 2020a; Lanzer et al. 2014; Teraa et al. 2016) A meta-analysis showed that calcification in any vascular bed is associated with a three to fourfold increased risk for cardiovascular events and mortality (Rennenberg et al. 2009).

We postulate that medial arterial calcification can aggravate CLTI and at the same time can be present in other vascular territories causing acute coronary syndrome or stroke. Halting the progression of these calcifications may improve the outcome of the patients.

The strongest inhibitor of vascular calcification in the body is inorganic pyrophosphate (PPi) (Evrard et al. 2015; Fleisch et al. 1965). Etidronate, the oldest bisphosphate is a stable PPi analogue, which has been used for the treatment of osteoporosis. It stops the vascular calcification in several rare monogenetic calcifying diseases and was effective in several RCT’s (Bartstra et al. 2020; Kawahara et al. 2013; Kranenburg et al. 2018; Oliveira and Oliveira 2016) A meta-analysis showed that the risk of cardiovascular mortality in patients treated with bisphosphonates decreased with 19% (RR 0.81; 95% CI 0.64–1.02) and that the risk of all-cause mortality decreased with 10% (RR 0.90; 95% CI 0.84–0.98) (Kranenburg et al. 2016).

Although there is evidence that etidronate is effective in improving proxy endpoints, both mechanistic studies and studies with clinically relevant endpoints are lacking in CLTI.

## Methods/design

This is an investigator-initiated double blind, placebo-controlled, randomized clinical trial comparing the effects of etidronate (*n* = 40) versus placebo (*n* = 40), taking a 25% dropout in to account, in patients with CLTI.

Our objective is to quantify the effects of etidronate on CT measured arterial calcification in patients with CLTI.

### Study population

Seventy-six patients with CLTI, stable for 2 weeks, will be recruited. After the screening for eligibility and explanation of the potential benefits and risks, the participants will sign the informed consent.

### Inclusion criteria

≥55 years old and stable CLTI for at least two weeksCLTI is defined as Fontaine stage 3 (rest pain and pain at night) or 4 (tissue loss)

### Exclusion criteria

eGFR < 30 ml/min/1.73 m2Osteomalacyabnormality of the esophagus interfering with the passage of the drugUse of bisphosphonates during the last 5 years

### Intervention and comparator

Subjects will be randomized to either treatment with etidronate orally for 12 months (cyclical 20 mg/kg for 2 weeks on and 10 weeks off) or placebo for 12 months (in a similar cyclical routine).

### Outcome parameters

*Primary outcome*: changes in arterial calcification in a total vascular score as quantified by CT-scan at baseline,6 months and at 1 year. Calcification will be quantified in the intracranial and extracranial carotid arteries, coronary arteries, thoracic and abdominal aorta and iliac, femoral and crural arteries. CT calcium volume will be quantified using dedicated applying a threshold of 130 Hounsfield Units for calcium.

*Secondary outcomes***:** numbers of amputations above and below the ankle, mortality, number of vascular interventions, quality of life as measured with the short form 36 (SF-36) health survey, serum calcium and phosphate and inorganic pyrophosphate.

### Sample size calculation and data analysis

We used data from the observational cohort study DIACART with type 2 diabetes patients with peripheral vascular disease, at least a history of cardiac disease, aged > 55 (Bourron et al. 2020). This cohort resembles our CLTI patient group as shown in the pooled data from our JUVENTAS and PADI studies in witch there were 281 CLTI patients included of whom 49.1% had diabetes type 2, 39% coronary disease, 22% TIA or stroke, 18% impaired renal function. At baseline the calcification score was median (IQR) 527 (55–2253) and at 31 months follow-up 1355 (167–4235) which amounts to 44% progression per year. The TEMP-study showed us (RCT etidronate/placebo in PXE patients) that etidronate completely halted the progression of calcification in all the main vascular beds. To be prudent we aim to find a difference between placebo and etidronate group after 1 year of 22%. Alfa 0.05%; Power 80%; Dropout rate 30%. Per arm 40 patients, total 80 will be included, taken into account a drop out of 25%.

Descriptive data will be presented as categorical (n, %) or continuous (mean ± standard deviation or median and interquartile range when appropriate).

Differences in change in CT calcification mass will be analyzed using unpaired Student’s t-tests or Mann-Whitney-U tests when appropriate.

Differences in change in secondary outcomes will be evaluated in similar manners.

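### The total sample size is given as both 76 and 80 and the dropout allowance as both 25% and 30%, so the text does not identify the evaluable number behind the 80% power

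*Protocol article*

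**What the plan says.** The protocol article gives the planned size in three places.

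- *Methods/design*: 40 patients on etidronate and 40 on placebo, "taking a 25% dropout in to account".
- *Study population*: "Seventy-six patients with CLTI, stable for 2 weeks, will be recruited".
- *Sample size calculation and data analysis*: "Alfa 0.05%; Power 80%; Dropout rate 30%. Per arm 40 patients, total 80 will be included, taken into account a drop out of 25" per cent. The 30% stands among the inputs, next to the alpha and the 80% power, and the next sentence gives 25% for the same total of 80.

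The target difference is 22% in one-year progression, half of the 44% per year derived from the observational cohort. The article gives neither the number per arm before the dropout allowance nor the SD of the change.

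**The concern.** There are two direct conflicts in current text: 76 against 80 for the total, and 30% against 25% for dropout. Screening losses cannot explain the first, because the number recruited cannot be smaller than the number included. The second occurs within two adjacent sentences about the same calculation.

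The total is the point at which recruitment ends. At 76 the trial is complete according to one section and four patients short according to two others. The dropout rate decides how many patients are expected to contribute a one-year CT. It is not a formality here: the article's own Background cites 18% mortality within a year in conservatively treated CLTI. Together the two figures set the evaluable number to which the 80% power refers.

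**Working it through.** **What can be reproduced.** The 80 cannot be rebuilt from the stated effect, because the article gives no SD. Only the dropout step can be checked. The pairing stated twice is consistent with itself: 30 / (1 − 0.25) = 40 per arm, total 80.

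**Evaluable numbers.** Evaluable per arm = (total / 2) × (1 − dropout).

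| Total | Dropout | Per arm | Evaluable total |
|---|---|---|---|
| 80 | 25% | 40 × 0.75 = 30 | 60 |
| 80 | 30% | 40 × 0.70 = 28 | 56 |
| 76 | 25% | 38 × 0.75 = 28.5 | 57 |
| 76 | 30% | 38 × 0.70 = 26.6 | 53.2 |

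**Which base could lie behind the two totals?**

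- Base 28: 28 / 0.70 = 40 per arm (80), and 28 / 0.75 = 37.3, rounded up to 38 per arm (76).
- Base 30: 30 / 0.75 = 40 per arm (80), and 30 × 1.25 = 37.5, rounded up to 38 per arm (76). The second step is the common but incorrect way to allow for 25% dropout.

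Each base yields both totals, so the printed figures do not tell them apart.

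**Size of the effect on power.** These assumptions are not in the article: a two-sided 5% test (alpha is printed as 0.05%, and no sidedness is given), an unpaired t-test (the article also allows Mann-Whitney), and an SD solved backwards from 80% power at the assumed base. With standardised difference d = 22 / SD, power comes from the noncentral t distribution with noncentrality d × √(n/2) and 2n − 2 degrees of freedom.

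| Evaluable per arm | Base 30 (d = 0.736, SD 22 / 0.736 = 29.9) | Base 28 (d = 0.762, SD 22 / 0.762 = 28.9) |
|---|---|---|
| 30 | 80.0% | 82.7% |
| 28.5 | 77.9% | 80.7% |
| 28 | 77.1% | 80.0% |
| 26.6 | 74.9% | 77.9% |

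**Cross-check by normal approximation.** For base 30, SD = 22 / [(1.960 + 0.842) × √(2/30)] = 30.4. Power = Φ(22 / [SD × √(2/n)] − 1.960), which gives 80.0%, 78.0%, 77.2% and 75.1% at 30, 28.5, 28 and 26.6 per arm. For base 28 the SD is 29.4 and power at 26.6 is 78.0%. The two methods agree to within about 0.2 points.

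**The case against.** The strongest reply is that the plan has a dominant reading. Forty per arm with 25% dropout is stated twice and is arithmetically exact for 30 evaluable per arm, whereas 76 and 30% each appear once and are never paired. On that view both are slips and 80 with 30 evaluable per arm is the plan. This is a fair guess, but only a guess: the 30% stands among the inputs to the calculation, and the same two totals also follow from a base of 28.

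Several stronger conclusions are tempting, and the document does not support them.

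- *The trial has only 75% power.* That needs 76 patients, 30% dropout and a base of 30 together, a plan stated nowhere.
- *The calculation rested on 28 per arm.* The document never states 28, and the route 30 × 1.25 explains 76 equally well.
- *The trial needs 86 patients.* 30 / 0.70 = 42.9, so 43 per arm, applies only if 30 evaluable are required, dropout is 30% and the full 80% must be kept.
- *The missing SD is itself the fault.* An article may leave it to the full protocol. Its absence only explains why a reader cannot settle the conflict from this text.

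It is also true that this is a proof-of-principle trial, and that the endpoint, the tests and the error rate are the same under either total. That limits the severity; it does not remove the contradiction.

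**Conclusion.** The point holds as an internal inconsistency of moderate severity. The article states two totals and two dropout rates without reconciling them, and the number per arm to which the 80% power belongs cannot be identified from it. Depending on the pairing, 53 to 60 patients would be evaluable.

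Under the assumptions shown, the cost is about 2 to 5 points of power if 30 per arm was the required number. If it was 28, the cost is about 2 points, and only for 76 patients with 30% dropout. The two contradictions rest on the text alone. The power figures depend on the assumed alpha, test and SD, and show only the order of the effect.

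**What to change.** State one total, one dropout rate and the resulting evaluable number per arm, in identical terms in Methods/design, Study population, and Sample size calculation and data analysis. The sponsor holds the calculation and can say which figures were used. If the evaluable number is below the one the calculation required, restate the power for that number rather than enrol more patients.

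The cost is a change of wording in three places. The stated power may fall by a few points. If 80 is the intended total, up to four more patients are recruited than the Study population section now states (80 − 76 = 4).

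### The only significance level in the protocol article is printed as 0.05% (0.0005), most likely a unit slip for 0.05 (5%), and should be confirmed and corrected before unblinding

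*Protocol article*

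**What the plan says.** The protocol article, section *Sample size calculation and data analysis*, lists three design inputs in one run: "Alfa 0.05%; Power 80%; Dropout rate 30" percent. The target effect is given just before: "we aim to find a difference between placebo and etidronate group after 1 year of 22" percent. It is set against an expected progression derived from an observational cohort, whose calcification score had a median (IQR) of "527 (55–2253) and at 31 months follow-up 1355 (167–4235) which amounts to 44% progression per year". The result is "Per arm 40 patients, total 80 will be included, taken into account a drop out of 25" percent.

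For the analysis, the same section says that differences in change will be "analyzed using unpaired Student’s t-tests or Mann-Whitney-U tests when appropriate". It attaches no significance threshold to those tests. No other section of the article states an alpha, and no standard deviation of the one-year change appears anywhere.

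**The concern.** A level of 0.05% is 0.0005. The two figures next to it, 80% power and 30% dropout, are ordinary percentages correctly scaled, so the percent sign after 0.05 cannot be put down to the layout of the line. It looks like a mix of two notations for the same thing, 0.05 and 5%.

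Two things are at stake. First, this is the only level on record in the article against which the primary result could be judged. Read as printed, a p-value of 0.01 for the change in calcification would be a negative result. Second, a correction made while the trial is blinded is clerical. The same correction made afterwards, with a primary p-value lying between 0.0005 and 0.05, could look like a relaxed threshold.

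**Working it through.** **Inputs from the article** (*Sample size calculation and data analysis*): alpha 0.05% as printed; power 80%; difference 22% at one year; 40 per arm; dropout given as both 30% and 25%; unpaired t-test or Mann-Whitney test. **Assumptions of this check:** two-sided test, t-test, and the 22% taken as 22 percentage points of change.

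**Step 1: what can be reproduced.** The annual progression can: (1355/527)^(12/31) − 1 = 0.441, the stated 44%. The target of 22 is half of that. The sample size cannot be reproduced at any alpha, because the formula

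n per arm = 2 (z₁₋α/₂ + z₀.₈₀)² (SD/difference)²

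needs an SD that is not given.

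**Step 2: evaluable patients.** 40 × (1 − 0.25) = 30 per arm; 40 × (1 − 0.30) = 28 per arm.

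**Step 3: back-solve the effect, assuming sizing at two-sided 0.05.** With z = 1.960 and 0.842 and n = 30, the standardized effect is d = (1.960 + 0.842) × √(2/30) = 0.723. The noncentral t gives 0.736. The implied SD is 22/0.736 = 29.9 points. With 28 per arm, d = 0.762 by the noncentral t.

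**Step 4: power for that same effect at two-sided 0.0005** (z = 3.481).
- Normal approximation, any n: Φ(1.960 + 0.842 − 3.481) = Φ(−0.679) = 24.9%.
- Noncentral t: 21.8% with 30 per arm, 21.6% with 28, 22.6% with 40.
- If both levels are one-sided, with 30 per arm: 18.7% (noncentral t) or 21.1% (normal).

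**Step 5: size needed for 80% power at 0.0005.** The normal approximation multiplies n by ((3.481 + 0.842)/(1.960 + 0.842))² = 2.38, so 30 × 2.38 = 71.4, or 72 per arm. The noncentral t gives 72.1, rounded up to 73 evaluable per arm. With 25% dropout that is 73/0.75 = 97.3, or 98 randomized per arm. Starting from 28 per arm, it is 67.3, rounded up to 68 evaluable.

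**Step 6: drop the assumption of Step 3.** For a 22-point difference and 30 evaluable per arm (two-sided t-test), power depends on the unstated SD:

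| SD (points) | Power at 0.05 | Power at 0.0005 |
|---|---|---|
| 18.7 | not tabulated | 80% |
| 20 | 99% | 71% |
| 25 | 92% | 40% |
| 30 | 80% | 22% |
| 35 | 67% | 12% |
| 40 | 55% | 7% |

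The stated 80% power is therefore compatible with alpha 0.05 at an SD near 30, and with alpha 0.0005 at an SD near 19. The article excludes neither.

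**The case against.** The strongest reply is that this is a misprint in a condensed article and that no calculation has been shown to be wrong. If 0.05% stands for 5%, the trial was sized at 5% and nothing here disturbs the stated power. If 0.0005 really was used, nothing in the article shows that 80% is wrong. The low power figure arises only for a trial sized at one level and tested at the other, and no section says that this will happen. This stands. A reader might infer from the printed alpha that 80 patients give only about 22% power, or that the stated power is false. The article does not support either statement, because it gives no SD, and an SD of about 18.7 points would deliver 80% even at 0.0005.

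It can also be said that alpha appears only as a sample-size input, that the sentences on analysis set no decision rule, and that a full protocol or analysis plan not shown here may state the level properly. That is fair, and it lowers the weight of the point. It does not remove it: the article prints a specific value, the value is very probably wrong, and the article contains no other. Silence on one- or two-sidedness, by contrast, is something an article may leave to fuller documents and is not held against it.

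**Conclusion.** The point holds as a correction to the text. The only significance level in the article is printed as 0.0005, almost certainly in place of 0.05, and as printed it would make any primary p-value between 0.0005 and 0.05 negative. That much needs no assumption.

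The size of the power loss is conditional. If the 80 patients were sized for 80% power at two-sided 0.05 with about 30 evaluable per arm, testing at 0.0005 would leave about 22% (noncentral t) to 25% (normal approximation), and about 73 evaluable per arm would be needed for 80%. These figures illustrate what the misprint would mean if followed. They do not show that the trial is underpowered. Since a unit slip is the likeliest cause, the sample size was probably calculated as intended, and the matter is a minor but necessary correction rather than a design flaw.

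**What to change.** Before unblinding, check the sample-size calculation for the alpha actually used. If it was 5%, change the printed value to two-sided alpha 0.05 (5%), or give the one-sided level if that was the one used. If 0.0005 was really intended, say so and state the SD that supports 80% power with 40 per arm. For a 22-point difference with 30 evaluable per arm, that SD is about 19 percentage points (18.7).

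The cost in the first case is one line of wording, with no change to sample size, data collection or choice of test. The same paragraph has to be edited anyway. It gives dropout first as "Dropout rate 30" percent and then as "taken into account a drop out of 25" percent, and the section *Study population* says "Seventy-six patients with CLTI, stable for 2 weeks, will be recruited" where the sample-size section has 80. Those are separate discrepancies, but one clean restatement of the calculation would settle all of them.

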## Discussion

Up to now, calcification of vessels in patients with CLTI has been considered the inert endpoint of vascular disease. This belief is based on cross-sectional studies that show extensive calcification in CLTI patients. Yet this type of study cannot differentiate between cause and effect.

So far, research has shown that calcification of the media is an active metabolic process independent of atherosclerosis. This calcification has shown to prevent remodeling and collateral formation in the cerebral circulation (Luijten et al. 2021) Thus, we believe there are reasons to reverse the present paradigm from ‘vascular disease causes calcification’ into ‘calcification cause vascular disease’. This can be proven in a clinical trial if stopping the calcification process improves the clinical outcome.

Etidronate halts the last step of the calcification process. It stops and even reverses the calcification process in nearly all vascular territories (Bartstra et al. 2020) and it decreases aortic stiffness (Kawahara et al. 2013) It also has an excellent risk profile. Yet whether this drug halts calcifications in CLTI is unknown and it is essential to plan a subsequent clinical study to show that etidronate is effective in clinical relevant endpoints.

The current trial focuses on mechanistic, so-called intermediate endpoints, but our main interest is to gain health benefit. Therefore, we already include secondary endpoints such as mortality, cardiovascular intervention of any type, amputation and quality of life. All participants will be followed during and after the trial for the occurrence of these endpoints. We hope to get our ‘mechanistic’ answer quickly and eventually will be able (after longer follow-up without treatment) to evaluate effects on endpoints that are most relevant for patients. This will provide us with the effect size of the treatment with etidronate in the CLTI group. To truly investigate an actual effect on clinical endpoints a phase 3 trial is needed with substantially larger numbers of participants and longer follow-up. The current proof-of-principle trial is the first step to assess efficacy and safety of etidronate in patients with CLTI.

This study may provide evidence that vascular calcification can be stopped with etidronate and may indicate that this could result in improved clinical outcome in CLTI and cardiovascular disease.

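### The change-score rule for secondary outcomes makes no exception for mortality, amputations and vascular interventions, which have no baseline and depend on time at risk

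*Protocol article*

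**What the plan says.** The section on sample size and data analysis gives one inferential rule, for the primary outcome: "Differences in change in CT calcification mass will be analyzed using unpaired" Student's "t-tests or Mann-Whitney-U tests when appropriate". The next sentence extends it: "Differences in change in secondary outcomes will be evaluated in similar manners". The only mention of categorical data in that section is descriptive: "Descriptive data will be presented as categorical (n, %) or continuous".

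The Outcome parameters section lists the secondary outcomes in a single run that opens with "numbers of amputations above and below the ankle, mortality, number of vascular interventions, quality of life as measured with the short form 36" and ends with serum calcium, phosphate and inorganic pyrophosphate. Event outcomes and continuous outcomes are not separated in either section.

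The Discussion says that participants are followed for the clinical events during and after the trial, and that the investigators "eventually will be able (after longer follow-up without treatment) to evaluate effects on endpoints that are most relevant for patients". It continues: "This will provide us with the effect size of the treatment with etidronate in the CLTI group". The sentence after that concedes that a larger and longer phase 3 trial is needed for clinical endpoints.

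**The concern.** Three of the listed outcomes do not fit the rule as written.

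- **No baseline.** A patient alive at randomisation has no baseline value of death to subtract. Amputations and interventions counted as trial outcomes start from zero for everyone. Taken literally, the rule cannot be carried out.
- **No time at risk.** Neither test uses length of follow-up or censoring. The article itself expects dropout (25% and 30% are both given) and cites 18% one-year mortality, so follow-up will differ between patients.
- **Death as a competing event.** A patient who dies early can have no later amputation or intervention. A raw count scores that patient as a good result, so an arm with more deaths can look better on amputations.

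At stake are the outcomes that the Discussion regards as most relevant to patients, and the clinical effect size that it promises.

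**Working it through.** The article gives no sample size or precision figure for the secondary outcomes, so there is none to reproduce.

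**Inputs from the article.** 40 patients per arm, 80 in total; dropout 25% or 30% (Sample size calculation and data analysis). One-year mortality 18% and amputation 27% under conservative treatment (Background).

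**Assumptions.** The Background rates apply to this trial; 0.4 events per patient-year for counts; annual mortality 18% versus 9% where the arms are made to differ; dropout 35% versus 15% where it is made unequal; follow-up of 3 and 5 years, since the article gives no length for the later phase.

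**1. Do the tests hold their level at 12 months?** Simulation of 20,000 trials with 40 per arm and no true difference, nominal level 5%:

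- death as 0/1 at 18%: 5.2% with either test
- amputation as 0/1 at 27%: 4.8% with either test
- counts at 0.4 per year with equal mortality: 5.1% (t-test), 5.4% (Mann-Whitney); overdispersed counts: 4.8% and 4.9%

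Power for 18% versus 9% mortality is 22.7% with either test, against 21.5% from the two-proportion formula. The level is sound and little power is lost.

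**2. What happens to counts when mortality differs?** The event rate while alive is 0.4 per year in both arms. With death hazard h = −ln(1 − annual mortality), the expected count is 0.4 × (1 − e^(−hT))/h.

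- T = 1: h = 0.198 gives 0.4 × 0.907 = 0.36; h = 0.094 gives 0.4 × 0.954 = 0.38. Rejection is 5.2% (t-test) and 5.4% (Mann-Whitney).
- T = 5: 0.4 × 3.17 = 1.27 against 0.4 × 3.99 = 1.60, a ratio of about 0.80 in favour of the arm with more deaths, although the rate ratio per year alive is 1. Rejection is 18% (t-test) and 20% (Mann-Whitney).

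**3. What happens to death as 0/1 under dropout?** Both arms have the same hazard.

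- One year, 25% dropout in each arm: the observed proportion is 15.8% instead of 18%; rejection 5.4%.
- One year, 35% versus 15%: 15.0% against 16.7%; rejection 5.7%.
- Three years, 35% versus 15%: rejection 6.8%.
- Five years, 35% versus 15%: 53.7% against 58.9%, where the true risk is 1 − 0.82^5 = 62.9%; rejection 8.1%.

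**4. How precise can the promised effect size be?** With 1:1 allocation, SE(log HR) ≈ 2/√events, and the 95% interval is the estimate times or divided by exp(1.96 × SE).

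- Deaths: 80 × 0.18 = 14.4; SE = 0.527; factor 2.8.
- Amputations: 80 × 0.27 = 21.6; SE = 0.430; factor 2.3.
- Range: at half the mortality (9%), 7.2 deaths give SE 0.745 and factor 4.3. With the 76 patients named under Study population, 13.7 deaths give factor 2.9.

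The t-test's own estimate is no sharper: the half-width for a risk difference at 18% is 1.96 × √(2 × 0.18 × 0.82/40) = 0.168, or about 17 percentage points either way.

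**The case against.** The best defence is one of scope. The sentence speaks of differences in change, and four listed outcomes do have a change: SF-36, calcium, phosphate and pyrophosphate. For these a t-test or Mann-Whitney test on change is ordinary and, under randomisation, unbiased. If the authors meant only those four, the method for events is merely unstated, and a condensed article may leave that to the full protocol or analysis plan. This reading is possible and lowers the severity. But the sentence covers the secondary outcomes without exception, and the list it refers to mixes both kinds. The stated rule therefore needs limiting whichever reading was meant.

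A reader might go further and infer that the tests are invalid for these outcomes. The 12-month results do not support that. Inflation appears only in the assumed scenarios of longer follow-up with unequal mortality or dropout, and the article does not say that these tests will be used for the later follow-up.

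A reader might also infer that no effect size can result. That is too absolute: a t-test gives a risk difference or a difference in mean counts. Only a Mann-Whitney test on its own gives no risk, rate or hazard ratio.

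Finally, the wide intervals are not caused by the choice of test. A Cox model on the same 14 deaths has the same limit, and the Discussion partly concedes it by calling for a larger trial. Nor does the article say that phase 3 will be sized from this estimate.

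**Conclusion.** The point holds as a badly fitting rule. Change is undefined for mortality, amputations and interventions, and the named tests take no account of time at risk, dropout or competing death. In a complete 12-month comparison, the cost is mainly in the estimate: a Mann-Whitney result carries no usable effect measure, and raw proportions understate risk under dropout (15.8% for a true 18% with 25% lost). Bias between arms is small at one year and grows with follow-up. In the assumed five-year scenarios, false rejection reaches 18–20% for counts with unequal mortality and 8% for death with unequal dropout.

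These sizes rest on the assumed event rate, mortality contrast, dropout contrast and follow-up lengths. The factor of 2.8 for mortality also assumes that rates from conservatively treated patients, counted from diagnosis, carry over to patients enrolled after two stable weeks.

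Severity is minor to moderate: the primary outcome and its sample size are untouched.

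**What to change.** Replace the sentence on secondary outcomes with a rule for each type:

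- **SF-36, calcium, phosphate, pyrophosphate:** ANCOVA of the follow-up value adjusted for baseline. This is a gain in precision over the change-score test, not the repair of an error.
- **Mortality:** Kaplan-Meier curves and a Cox hazard ratio with 95% CI.
- **Time to first amputation:** analysis with death as a competing event. This draws on a listed outcome and adds no composite endpoint.
- **Numbers of amputations and of vascular interventions:** Poisson or negative binomial rate ratio with log follow-up time as offset, reported alongside mortality, because an offset alone does not show whether fewer events came with more deaths.

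State that the same methods apply to the follow-up after treatment. In the Discussion, describe the clinical effect size as an exploratory estimate with its 95% CI, and say that its width is set by the small number of events.

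Cost: dates of death, amputation, intervention and last contact must be recorded, and the analysis becomes slightly more complex. Design, sample size and primary analysis do not change.
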